## Abstract

**Background:**

Cardiac arrest affects 30-35, 000 hospitalised patients in the UK every year. For these patients to be given the best chance of survival, high quality cardiopulmonary resuscitation (CPR) must be delivered, however the quality of CPR in real-life is often suboptimal. CPR feedback devices have been shown to improve CPR quality in the pre-hospital setting and post-event debriefing can improve adherence to guidelines and CPR quality. However, the evidence for use of these improvement methods in hospital remains unclear. The CPR quality improvement initiative is a prospective cohort study of the Q-CPR real-time feedback device combined with post-event debriefing in hospitalised adult patients who sustain a cardiac arrest.

**Methods/design:**

The primary objective of this trial is to assess whether a CPR quality improvement initiative will improve rate of return of sustained spontaneous circulation in in-hospital-cardiac-arrest patients. The study is set in one NHS trust operating three hospital sites. Secondary objectives will evaluate: any return of spontaneous circulation; survival to hospital discharge and patient cerebral performance category at discharge; quality of CPR variables and cardiac arrest team factors. Methods: All three sites will have an initial control phase before any improvements are implemented; site 1 will implement audiovisual feedback combined with post event debriefing, site 2 will implement audiovisual feedback only and site 3 will remain as a control site to measure any changes in outcome due to any other trust-wide changes in resuscitation practice. All adult patients sustaining a cardiac arrest and receiving resuscitation from the hospital cardiac arrest team will be included. Patients will be excluded if; they have a Do-not-attempt resuscitation order written and documented in their medical records, the cardiac arrest is not attended by a resuscitation team, the arrest occurs out-of-hospital or the patient has previously participated in this study. The trial will recruit a total of 912 patients from the three hospital sites.

**Conclusion:**

This trial will evaluate patient and process focussed outcomes following the implementation of a CPR quality improvement initiative using real-time audiovisual feedback and post event debriefing.

**Trial registration:**

ISRCTN56583860

## Background

Each year approximately 30-35, 000 people sustain a cardiac arrest in hospitals in the UK. National audits in the UK and US report an initial survival rate of 50-60%[1,2]. Morbidity and risk of death are high in the first few days after cardiac arrest, however, after this high risk period has passed, the majority (80%) of people are relatively free from on-going morbidity and are alive at one year.

The International Liaison Committee for Resuscitation (ILCOR) have developed evidence based guidelines for resuscitation which are used across NHS trusts [3]. However these can only improve outcomes if they are successfully implemented into clinical practice [4].

The importance of the quality of CPR has been reinforced in a series of observational studies in humans. Chest compression depth [5,6]; rate [7]; ventilation rate [8] and duration of pre-shock pauses [6,9] have all been shown to influence the likelihood of a successful resuscitation attempt. Despite these compelling data, observational studies during real life resuscitation attempts consistently demonstrate sub-optimal implementation of resuscitation guidelines in practice [10,11].

The integration of real-time audio/visual feedback during actual CPR improves the quality of CPR in pre-hospital resuscitation attempts [5,12], but it's effect in hospital has been less clearly demonstrated [13]. The use of post event debriefing in simulator based CPR training significantly improves team performance [14,15] and is widely used in military and aviation practices for improving future performance. Junior doctors have also reported feeling un-prepared and concerned about managing cardiac arrest and have called for more feedback on their performance [16]. Systems of post-event debriefing of the cardiac arrest team of real life resuscitation atempts were associated with improved: knowledge; adherence to guidelines; quality of CPR and a significantly increase in survival (44% to 60%, P = 0.03)[17].

This promising study has some limitations and it is unclear if these findings could be directly extrapolated to clinical practice. Firstly, the historical control group preceded a major change in resuscitation guidelines (Guidelines 2005), so it is unclear if the improvement in survival was contaminated by the change in practice. Secondly, the casemix in this study are significantly different from UK practice (63% of arrests occurred in a critical care area as opposed to 11% in our own Trust and 15% nationally). Thirdly, CPR feedback technology was already in widespread use with the control cohort, which is rare in the UK at present.

In the recent ILCOR knowledge gaps and research prioritisation exercise, the paucity of evidence in this area was identified and the need for further research on feedback during and after CPR was prioritised [18]. The aim of this project is to test whether implementation of a CPR quality initiative (comprising of real-time CPR feedback technology supplemented with post-event debriefing) affect patient and process focused outcomes.

## Methods/Design

### Trial Approvals and Conduct

The trial is approved by the Coventry Research Ethics committee. The trial is registered on the International Standard Randomised Controlled Trial Registry (ISRCTN56583860). It will be carried out in accordance with the Medical Research Council (MRC) Good Clinical Practice Guidelines [19], applicable UK legislation and the Standard Operating Procedures of the Department of Anaesthesia, Critical Care, Pain and Resuscitation. The sponsor organisation for the trial is Heart of England NHS Foundation Trust. The trial is funded by the National Institute for Health Research (NIHR) Research for Patient Benefit (RfPB) Programme. The full trial protocol can be found in Additional File 1.

### Outcome Measures

The primary outcome for the trial is intial cardiac arrest survival (defined as sustained (> 20 minutes) return of spontaneous circulation). The secondary outcomes are split into two categories; patient focused and process focused outcomes. The patient focused outcomes include: any return of spontaneous circulation; survival to hospital discharge and cerebral performance category of patients at discharge. The process focussed outcomes focus on both quality of CPR and team factors. Quality of CPR outcomes are: quality of 2222 call; chest compression depth; chest compression rate; no-flow time; no-flow time adjusted; duration of pre-shock and post shock pause; ventilation rate; time to first shock (if initial rhythm VF/VT) and appropriate decision to shock. Team factors are; CPR knowledge amongst the cardiac arrest team and confidence/preparedness.

### Eligibility Criteria

Consecutive hospitalised adult patients who sustain a cardiac arrest during their hospital stay will be eligible for inclusion in the study according to the following criteria.

Individual patients will be eligible if:

1. The patient is known or believed to be aged 18 years or over.

2. The patient sustains a cardiac arrest and resuscitation is attempted (defined as loss of a pulse requiring the delivery of chest compressions).

Exclusion criteria will be:

1. If the patient has a Do-not-attempt resuscitation order written and docummented in their medical records

2. The cardiac arrest is not attended by a resuscitation team

3. If the cardiac arrest occurs out-of-hospital

4. Previous participation in this study

### Power and Sample Size

The sample size estimation is based on a baseline return of spontaneous circulation rate of 44% (from the last 12 month audit at the Trust). To predict a 16% absolute improvement in ROSC rate (as seen in the Edelson et al [17] study which had a similar baseline rate as our Trust) 152 patients will be required in each arm to achieve 80% power at a significance level of 0.05.

Secondary outcomes: Based on the data from the Edelson study and our own preliminary studies (n = 6); the study will have sufficient power (80%) at a significance level of 0.01 to detect the following improvements in CPR quality performance data (all figures are relative changes from baseline): chest compression depth (8%); ventilation rate (12%); no flow fraction (18%); appropriate decision to shock (15%).

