### Rationale for study design

The use of the initial control phase at all sites enables within-site comparison of each intervention with standard care, while the inclusion of Solihull as a control site allows the estimation of the effect of the interventions to be adjusted for changes over time due to changes in other aspects of resuscitation care.

The prospective cohort approach has been chosen because of the risk that the significant learning effect from the feedback amongst the cardiac arrest team could contaminate the results if procedures were individually randomised to the two new interventions or the control. This learning effect would similarly limit the applicability of a cross over trial as a prolonged wash-out period between interventions would be required and even this would not guarantee that any learning from the intervention would not be retained by participants.

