### Guidelines change in 2010

The International Liaison Committee for Resuscitation and European Resuscitation Council (UK) published new resuscitation guidelines on 18^th ^October 2010. These were incorporated into clinical practice by the trust in December 2010. The Q-CPR feedback devices will be updated to coincide with the adoption of the new guidelines before the implementation phase begins. The control site (Solihull) will allow for estimation of the interventions to be adjusted for changes due to the new guidelines.

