### Statistical Analysis

Baseline patient characteristics such as age, sex, aetiology of admission illness, pre-existing illnesses and time of arrest will be summarised for patients at the three hospital sites. Characteristics of patients at the three sites will also be compared. Chi-squared tests will be used for binary variables. Following an assessment of whether they are normally distributed, continuous variable will be compared using linear (ANOVA) models (possibly after transformation) or non-parametric tests.

Binary responses such as the primary outcome of survival for > 20 minutes and the patient-focussed secondary endpoints of return of spontaneous circulation, survival to hospital discharge and cerebral performance at discharge dichotomised to divide patients into two groups will be analysed using a logistic regression approach. The analysis will use data from both phases of the study, with a model that includes a period effect and centre effects. This will allow estimation and testing of hypotheses regarding the effect on the survival rate etc. for the three different intervention arms adjusted for differences between the sites and changes over time. The effect of intervention will also be adjusted for baseline patient characteristics. The effect of intervention will first be fitted as a factor with three levels. If this effect is significant at the p = 0.05 level, further models will be fitted including contrasts to enable pairwise comparisons of the different interventions.

Continuous responses such as the process-focussed secondary outcomes will be analysed using linear regression (ANCOVA) models, possibly after transformation to ensure that the assumption that the residuals from the fitted models are normally distributed is reasonable. As for logistic regression analyses described above, the comparison of the interventions will be adjusted for baseline patient characteristics and differences over time and between the three sites.

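### The stated 80% power belongs to an unadjusted two-group comparison; at 152 patients per site and phase the planned centre-plus-period model has about 50%

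*Protocol article*

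**What the plan says.** The Power and Sample Size section starts from a "baseline return of spontaneous circulation rate of 44" per cent, aims at a 16-point absolute rise, and concludes that "152 patients will be required in each arm to achieve 80% power at a significance level of 0.05". The Abstract states: "The trial will recruit a total of 912 patients from the three hospital sites". Since 912 = 6 × 152, an arm here is one site in one phase (three sites, two phases; Table 1).

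The Statistical Analysis section analyses the primary outcome by logistic regression on both phases together, "with a model that includes a period effect and centre effects". Intervention enters first as a three-level factor, and pairwise contrasts follow only if that factor is significant at 0.05.

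The Rationale for study design gives the control phase and the control site separate purposes. The initial control phase "enables within-site comparison of each intervention with standard care", and Solihull is there so that effects can be adjusted for change over time. The section on the 2010 guideline change adds: "The control site (Solihull) will allow for estimation of the interventions to be adjusted for changes due to the new guidelines".

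**The concern.** The sample size compares two groups. The primary analysis estimates each intervention effect from four groups, because the before/after change at Solihull is subtracted from the change at the intervention site. That subtraction protects against confounding by time, which matters here because new resuscitation guidelines entered Trust practice in December 2010, before the implementation phase. It costs precision, and the power statement makes no allowance for it.

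The trial therefore carries an 80% figure that its primary analysis does not have. A non-significant result could be taken as the result of a well-powered trial and so as evidence against a 16-point effect, when the planned test would miss that effect about half the time.

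**Working it through.** **Inputs.** Control rate 0.44, intervention rate 0.60, significance level 0.05, target power 80% and 152 per arm (Power and Sample Size); total 912 (Abstract); 2007 arrests of 297 at Heartlands, 186 at Good Hope and 168 at Solihull, 13-month phases at Heartlands and Good Hope, and 80% enrolment at Solihull (Sample Size Feasibility). The test is taken as two-sided, which is the reading that reproduces 152; one-sided gives 120.

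**1. The plan's own figure.** Two proportions, pooled variance, no continuity correction:

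n = [1.96·√(2·0.52·0.48) + 0.8416·√(0.44·0.56 + 0.60·0.40)]² / 0.16² = 151.9, so 152 per group.

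The stated figure reproduces exactly.

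**2. What the planned model estimates.** An intercept, two centre terms, one period term and two intervention terms make six parameters for six site-phase cells. Before covariates the model is saturated, so the four control cells cannot be pooled to gain precision. Each intervention-versus-control log odds ratio is

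(logit after − logit before, intervention site) − (logit after − logit before, Solihull).

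**3. Power for one contrast at 152 per cell.** Assume 44% in every control cell and no period change.

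- Effect: logit(0.60) − logit(0.44) = 0.647.
- Variance: 3/(152·0.2464) + 1/(152·0.24) = 0.0801 + 0.0274 = 0.1075. Two cells alone would give 1/(152·0.2464) + 1/(152·0.24) = 0.0541, so the variance doubles.
- SE = √0.1075 = 0.328; z = 0.647/0.328 = 1.97.
- Power = Φ(1.97 − 1.96) ≈ 50%. On the risk-difference scale it is 51%.

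**4. Through the three-level test.** Simulation of the six binomial cells (200,000 replicates), 152 per cell:

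| Event | Power |
|---|---|
| One named contrast, no prior test | 50% |
| Three-level (2-df) test alone | 52% |
| Three-level test passed and one named contrast significant | 42% |

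The figures are almost the same whether both interventions work or only the named one does. If one intervention has the full 16 points and the other half of that, the 2-df test has about 41% and the joint event for the full-effect intervention about 38%.

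**5. What would give 80%.** For one contrast, n per cell = (1.96 + 0.8416)²·(3/0.2464 + 1/0.24)/0.647² ≈ 307, about 1,842 in all. With 152 per cell, solving the formula in step 3 for 80% power gives an intervention rate of 66.5%, a rise of 22.5 points.

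**6. If recruitment exceeds 152.** Cell size = 2007 count × 13/12 × capture rate, with Solihull assumed to run the same 13 months:

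| Capture | Heartlands / Good Hope / Solihull per phase | Single contrast, Heartlands | Single contrast, Good Hope |
|---|---|---|---|
| 80% | 257 / 161 / 146 | 59% | 51% |
| 100% | 322 / 202 / 182 | 68% | 60% |

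With both interventions effective, the joint figures (three-level test passed and that contrast significant) are about 49% and 44% at 80% capture, and about 60% and 54% at 100%. Solihull, the smallest site, limits the precision of both contrasts.

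**The case against.** The strongest reply has four parts.

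- **The arithmetic is right, and a comparison exists for which 80% holds.** The Rationale for study design names a within-site comparison as one purpose of the control phase, and 152 before against 152 after at one site does have 80% power. The protocol says that Solihull allows adjustment for the guideline change; it does not say that adjustment is obligatory. All of this stands. But the Statistical Analysis section assigns the adjusted model to the primary outcome, and the power statement is attached to the trial without qualification. The Background also faults the earlier debriefing study because its historical controls preceded a guideline change, and an unadjusted before/after test here would share that weakness.
- **The 50% and 42% assume exactly 152 per cell.** Eligible patients are consecutive and the feasibility section expects to capture all of them, so cells may be larger. That is fair, and the larger-cell figures should be reported too. They stay below 80%.
- **The 42% is a specific joint event.** It is not the power of the three-level test, which is about 52% at 152 per cell and about 65% at full capture with both interventions effective. The distinction is correct and should be kept.
- **The article is condensed, and how readers would take a null result is a prediction.** Both are true. But the two sections at issue are explicit and do not match, so this is not a detail left to the full protocol.

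Covariate adjustment is planned, but the protocol claims no gain from it, and it would have to offset a doubled variance.

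**Conclusion.** The concern holds. The calculation is correct for its own formula; the fault is that the formula does not belong to the planned primary analysis. At 152 per site and phase, the model has about 50% power for a 16-point effect of one intervention against control, and about 42% once the three-level test must also be passed. With all arrests over 13 months, single-contrast power is 59–68% at Heartlands and 51–60% at Good Hope for 80–100% capture. No recruitment reading examined reaches the stated 80%.

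These figures assume two-sided testing at 0.05, a 44% rate in all control cells, no gain from covariates, the same window at Solihull where larger cells are used, and no site-by-period variation beyond binomial sampling. Any such extra variation would lower power further.

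**What to change.** Restate the power paragraph for the model in the Statistical Analysis section:

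- at 152 per site and phase, about 50% power for a 16-point difference in one intervention-versus-control contrast, and about 42% when the three-level test must be passed first;
- a detectable rise of about 22.5 points (44% to 66.5%) with 80% power for one contrast;
- the corresponding figures for consecutive enrolment over 13 months, with the capture rate and the Solihull window stated;
- a sentence that 80% applies only to an unadjusted before/after comparison within one site, which is not the primary analysis.

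Carry the same statement into the full protocol and the analysis plan. The cost is wording and a less favourable stated power. Model, design and recruitment are unchanged.

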### Sample Size Feasibility

The number of documented cardiac arrests across the 3 in-patient hospital sites was recorded as 651 in 2007 (Heartlands 297; Solihull 168; Good Hope 186). We propose to run the control phase and intervention phase at Heartlands and Good Hope for 13 months each. Patients sustaining a cardiac arrest on more than one occasion were not included in this audit. Cardiac arrest event data are used as a quality indicator by the Trust, so based on our current experience we anticipate that the data informing the primary outcome of the study (survived event) will be complete. Although we anticipate capturing all eligible cardiac arrests, we have based our recruitment windows assuming an 80% enrollment rate at the smallest centre (Solihull).

### Consent

Prospective consent from research participants prior to enrolment is impossible in this trial; the occurrence of a cardiac arrest is unpredictable, and a victim becomes unconscious within seconds. Treatment (in the form of CPR) must be started immediately in an attempt to save the person's life. It is therefore not practical to consult a carer or independent clinician without causing the potential participant harm as a result of delaying treatment. Conducting research in emergency situations where a patient lacks capacity is regulated by the Mental Capacity Act (2005) in England and Wales and the Adults with Incapacity Act (2000) in Scotland. The relevant ethics committees have determined that the research methods are compliant with the requirements of this legislation.

Process and outcome data are routinely recorded on the Trust clinical CPR audit database. Data for analysis for research purposes will be extracted and anonomised from this database.

Regretably the nature of the emergency in question mean that the majority (> 80%) of resuscitation attempts will be unsuccessful. Our experience of approaching relatives in the hours and days after a cardiac arrest has been that this causes distress and confusion at a time when they are already burdended by either the loss of a loved one or shock of a sudden deterioation in health status. Our assessment of the burdens of approaching relatives or patients for consent to use anonymised data which are already routinely collected outweigh the benefits.

### Protection against Bias

It is not possible to blind either the cardiac arrest team or investigator team from the study intervention. The following steps will be taken to protect against bias. The primary and secondary patient focused outcomes are objective outcomes that cannot be influenced by knowledge of the treatment allocation. The CPR performance and electrocardiographic data are collected electronically directly from the study defibrillators after resuscitation attempts and are therefore not subject to bias. Researchers measuring parameters requiring interpretation from Q-CPR (% correct shock decisions, pre and post-shock pauses) will be blinded from knowing whether the data are from the control or intervention site.

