### Trial Intervention/Treatments

This study will be a prospective, cohort study. The study will evaluate two interventions: real-time audio-visual feedback during CPR and real-time audio-visual feedback during CPR plus post event feedback using the Q-CPR system (described below). We have not included a 3rd arm (post event feedback alone) as this would be unlikely to be used in clinical practice as to be able to provide this model of post event feedback requires the use of the Q-CPR equipment, which incorporates the real-time audiovisual feedback facility.

The study will be divided into 2 phases (see table 1). During the first phase, baseline data will be collected at each site without any intervention. During the second phase, real-time feedback phase will be implemented at one site (Good Hope-GH) and real-time audiovisual feedback plus post event debriefing at one site (Heartlands-BHH). The remaining site (Solihull-SH) will act as the control site during both interventions. The purpose of the control site is to exclude any Trust-wide or other temporal changes in care as potential explanations for any changes in outcomes at Heartlands/Good Hope.

**Table 1 T1:** Showing the two phases and interventions at the 3 hospital sites

Site	Phase 1	Phase 2
**GHH**	Control	Realtime audiovisual feedback only

**BHH**	Control	Realtime audiovisual feedback plus post event debriefing

**SH**	Control	Control

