### The Q-CPR system

Existing Trust defibrillators (MRX, Phillips, UK) will be upgraded with Q-CPR technology (Figure 1). Briefly, a 10 × 5 cm device (containing an acceleratometer and force detector) is placed on the patient's chest during resuscitation and measures chest compression parameters. Real-time audio and visual feedback is provided on chest compression rate, depth, incomplete release and duration of interruptions in chest compression. Ventilation rate is calculated from changes in transthoracic impedance measured through the defibrillator pads. The technical details and validation of this device have been previously published [10]. The CPR-review facility captures and exports these data along with continuous ECG, transthoracic impedance and voice recordings of the resuscitation attempt, thus providing audio and detailed visual data about the resuscitation attempt, without the need for potentially cumbersome video recording equipment.

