### Real-time feedback

The Q-CPR system will be used to provide real-time audio and visual feedback. Audio feedback comprises spoken messages that are corrective when the performance of CPR deviates from a defined list of parameters. Examples of voice prompts include: 'Blow in more air'; 'Press down deeper'; 'Switch over faster to compressions'. Visual feedback provides information on the adequacy of chest compression depth, compression and ventilation rates and the duration of interruptions in CPR.

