### Q-CPR interrogation

Objective CPR performance and ECG data will be downloaded from the study defibrillators and analysed using Q-CPR review software (Phillips, UK). Cardiac rhythm at the start of the resuscitation, as well as before and after defibrillation will be extracted from ECG recordings. The defibrillator will be configured to record CPR quality parameters (compression rate, depth, ventilation rate, no-flow fraction (which represents the fraction of time within a given period that a pulseless patient went without chest compressions) [20]. The duration of pre and post-shock pauses will be calculated manually from the ECG and compression depth waveforms. The time to first shock (for patients initially presenting in a shockable rhythm) will be derived from the time of the cardiac arrest call (recorded at the central switchboard) with the time of shock delivery. The Trust defibrillators are synchronised on a monthly basis with the central switchboard time which achieves a co-efficient of variation in times of < 2%.

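### Reader blinding for shock decisions and shock pauses is defined by site, although exposure depends on site and phase together

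*Protocol article*

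**What the plan says.** The Protocol article, under Protection against Bias, accepts that neither the arrest team nor the investigators can be blinded to the intervention. It singles out a small group of outcomes for blinded reading: "Researchers measuring parameters requiring interpretation from Q-CPR (% correct shock decisions, pre and post-shock pauses"). Those readers "will be blinded from knowing whether the data are from the control or intervention site". Phase is not mentioned.

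Under Trial Intervention/Treatments, "During the first phase, baseline data will be collected at each site without any intervention". Table 1 then assigns real-time feedback to Good Hope and feedback plus debriefing to Heartlands in Phase 2, with Solihull a control throughout. Rationale for study design presents the initial control phase as the basis for comparing each intervention with standard care within a site, and uses Solihull to adjust for time.

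On the material available to readers, The Q-CPR system says that the review facility "captures and exports these data along with continuous ECG, transthoracic impedance and voice recordings of the resuscitation attempt". Real-time feedback says: "Audio feedback comprises spoken messages that are corrective when the performance of CPR deviates from a defined list of parameters". Q-CPR interrogation says that the data are "downloaded from the study defibrillators and analysed using Q-CPR review software", and then names narrower sources: "The duration of pre and post-shock pauses will be calculated manually from the ECG and compression depth waveforms", and "Cardiac rhythm at the start of the resuscitation, as well as before and after defibrillation will be extracted from ECG recordings".

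Monitoring of Data Quality adds that rhythm and shock pauses are measured by two researchers, that their agreement is reported, and that the same two settle disagreements by re-review and consensus.

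**The concern.** Blinding of outcome readers protects a comparison only if it conceals the variable on which the comparison is made. Here that variable is the site-by-phase cell, not the site. At Heartlands and Good Hope the same site supplies both control and intervention records, so a rule that hides the site but not the phase leaves the before-and-after contrast at those sites open to a reader's expectations.

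The outcomes at stake are those that the plan itself says need interpretation. Appropriate decision to shock is also one of four secondary outcomes with a stated detectable change (15% relative, at the 0.01 level, under Power and Sample Size). A reader who expects better performance after implementation could call borderline shock decisions or pause boundaries more favourably in Phase 2.

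The voice channel is a second, conditional route. If a reader plays the audio of an intervention-phase record and a prompt is audible, feedback status is revealed whatever has been done about site and date labels.

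**Working it through.** The point is mainly one of text against text, with simple counting to show what knowledge of phase gives away.

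**Step 1: what defines exposure.** From Table 1:

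| Site | Phase 1 | Phase 2 |
|---|---|---|
| Good Hope | control | feedback |
| Heartlands | control | feedback plus debriefing |
| Solihull | control | control |

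Two of the six cells are intervention cells. Two of the three sites change status between phases, so the label *control or intervention site* fixes exposure only at Solihull, or once the phase is also known.

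**Step 2: what the stated masking covers.** Site is covered. Phase, date and feedback status are not named. Under Data Collection, the date and location of each arrest are among the fields passed to the research team, and the article does not say whether the readers are kept from them.

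**Step 3: what a reader masked to site but aware of phase can infer.** The inputs are 152 per arm (Power and Sample Size) and 912 in total (Abstract). Six cells of 152 reproduce the total: 6 × 152 = 912. Taking the cells as equal:

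- Knowing nothing: 2 × 152 / 912 = 304 / 912 = 33% chance that a record is intervention.
- Knowing it is Phase 1: 0 / (3 × 152) = 0 / 456 = 0%.
- Knowing it is Phase 2: 304 / 456 = 67%.

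Phase alone therefore moves the reader from 33% to either certainty of control or two-to-one odds on intervention.

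**Step 4: what the audio could add.** The export includes voice recordings and the intervention includes spoken prompts. That prompts can be heard on the recordings is a reasonable inference, not something the article states. The 304 intervention-phase records are an upper bound on the files that audio could unmask. Prompts sound only when performance leaves the set limits, so some files may contain none. Shock pauses exist only where a shock was given, and the article gives no shocked fraction.

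**Step 5: which outcomes depend on these readers.** Shock decisions and pre- and post-shock pauses do. Sustained return of circulation (the primary outcome) does not. Nor do compression depth, compression rate, ventilation rate and no-flow fraction, which the defibrillator records.

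**The case against.** Four arguments weigh on the other side.

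*The sentence plainly intends to hide intervention status, and Table 1 labels each cell as control or intervention.* The intention is clear, but the wording names the site. A data manager who followed it literally could remove site labels and leave dates in place. This makes it a safeguard to be restated, not evidence that phase will in fact be visible.

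*If site is truly hidden, a reader's shift in all Phase 2 records would also fall on Solihull, and the period effect in the model would absorb it.* This largely stands for the adjusted intervention effect, provided that the shift is common to all sites on the model's scale. It does not protect the within-site comparison that the rationale section relies on. It also fails if anything in the file, such as an audible prompt, separates Solihull's Phase 2 records from the others.

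*File preparation is operational detail that an article leaves to the full protocol.* This is fair as regards audio and file order, and the full protocol (Additional File 1) may deal with both. It does not answer the main point, because the article states the masking rule and states it by site.

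*Dual reading already protects these outcomes.* It is a real second safeguard for rhythm and pauses, so blinding is not the only protection. But two readers with the same expectation can agree and both be biased, and consensus between the same two people does not remove a shared bias.

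A reader might also infer that the voice recordings defeat the blinding outright. The documents do not support that. The named sources are ECG and compression-depth waveforms, and nothing says that readers receive or play the audio.

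**Conclusion.** The point holds as a mismatch between a stated safeguard and the design. Blinding is specified by site, exposure is set by site and phase together, and the before-and-after comparison at Heartlands and Good Hope is not covered by the wording. The voice recordings are a possible further route to unmasking, conditional on readers playing them.

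The reach is limited to the interpreted secondary process outcomes; the primary outcome is untouched. The size of any reader bias cannot be derived from the article. The 33% and 67% figures describe what a reader could guess, not bias, and assume six equal cells of 152. Shares based on expected site volumes would need further assumptions, because the article gives 13-month phases only for Heartlands and Good Hope and the 80% enrolment rate only for Solihull.

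It would be wrong to conclude that a third of the records will be unmasked, or that the blinding has failed. The supported conclusion is that the rule as worded does not mask the phase contrast and is cheap to correct before reading begins.

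**What to change.** In Protection against Bias, change the masking statement so that readers of shock decisions and shock pauses are *blinded to site, phase and feedback status*.

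To make that workable, give the readers waveform and ECG files with the audio and any feedback markers removed, and with date, site and device identifier replaced by a study number. Present the files in random order, mixing both phases and all three sites. Keep the two-reader procedure as it is.

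The cost is one additional de-identification step at export, which existing data staff can do. Readers lose some audio context, but the loss should be small because the article already names waveforms and ECG as the material to be read.
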